**5.2 Dosing Delays / Dose Modifications**

Prior to re-treatment, patients must have recovered the following organ function:

- absolute neutrophil count 1.0 x 109/l
- platelets 100 x 109/l
- total bilirubin < 2 x upper limit of normal
- AST (SGOT) / ALT (SGPT) 2.5 x upper limit of normal
- creatinine 1.5 x upper limit of normal
- other Grade 0-1
- Patients should be dose reduced to 400mg po in AM and 200mg po in PM in the event of any of the following:
- Nausea or vomiting dose reductions should only be in the face of maximal anti-emetic therapy
- Grade 4 non-hematologic toxicity: if study drug related patients should be taken off study
- Grade 3 non-hematologic toxicity: hold BAY43-9006 and reevaluate patient weekly until toxicity improves to < Grade 1. Reduce dose by 200 mg /day and no more than 2 dose reductions allowed.
- Increased liver functions (Grade 3-4): withhold treatment until resolved to < grade 1 toxicity and decrease by 200 mg.
- Grade 4 hematologic toxicity: withhold treatment until resolvedto < grade 1 toxicity and decrease by 200 mg. If Grade 4 neutropenia lasts for more than 7 days after therapy with growth factor support contact PI.
- Many patients will have a rash that will require drug withdrawal and toxicity resolution before restarting. Hand-foot syndrome will require drug withdrawal and reduction

Management of Treatment-emergent Hypertension:

| **Grade of Event (CTCAE v.3)** | **Management/ Next Dose** |
| --- | --- |
| grade 1 | Consider increased BP monitoring |
| grade 2 asymptomatic and diastolic BP < 110 mm Hg | Begin anti-hypertensive therapy and continue agent |
| grade 2 symptomatic/ persistent  OR  diastolic BP ≥ 110 mm Hg  OR  grade 3 | 1. Agent should be held* until symptoms resolve  and diastolic BP ≤ 100 mm Hg; also  treat patient with anti-hypertensives and when  agent is restarted, reduce by 1 dose level.**  2. If diastolic BP not controlled (≤ 100) on  therapy, reduce another dose level *** |
| grade 4 | Discontinue protocol therapy |
| * Patients requiring a delay of > 2 weeks should go off protocol therapy.  ** May be able to resume full dose later.  *** Patients requiring > 2 dose reductions should go off protocol therapy. | |

Current CTCAE definitions used by CTEP:

Grade 1: asymptomatic, transient (< 24 hours) increase by > 20 mmHg (diastolic) or to

>150/100 if previously WNL; intervention not indicated

Grade 2: recurrent or persistent (> 24 hours) or symptomatic increase by > 20 mmHg

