(diastolic) or to > 150/100 if previously WNL; monotherapy may be indicated

Grade 3: requiring more than one drug or more intensive therapy than previously

Grade 4: life threatening (e.g. hypertensive crisis)

Patients will be allowed 3 weeks for resolution of toxicity. Treatment will be discontinued if any grade 3 or 4 toxicity does not resolve in 3 weeks.

No patients should have his / her dose re-escalated following dose reduction.

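### Section 5.2 both allows and forbids a return to full dose after a hypertension reduction, and two narrower overlaps (length of hold, grade 4 liver toxicity) have no stated precedence

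*Protocol*

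**What the plan says.** All the relevant text is current wording in protocol section 5.2.

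- **Re-escalation.** In the row of the hypertension table that requires a hold, the agent is restarted with the instruction "reduce by 1 dose level". The footnote to that instruction reads "May be able to resume full dose later". The section ends with "No patients should have his / her dose re-escalated following dose reduction".
- **Length of hold.** Another footnote to the same row reads "Patients requiring a delay of > 2 weeks should go off protocol therapy". The text after the table reads "Patients will be allowed 3 weeks for resolution of toxicity" and continues "Treatment will be discontinued if any grade 3 or 4 toxicity does not resolve in 3 weeks".
- **Grade 4 liver toxicity.** One bullet reads "Grade 4 non-hematologic toxicity: if study drug related patients should be taken off study". A later bullet in the same list begins "Increased liver functions (Grade 3-4): withhold treatment until resolved" and goes on to a 200 mg decrease.
- **Lead-in to the list.** A line above these bullets gives a single reduced dose, 400 mg in the morning and 200 mg in the evening, for every event listed below it.

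Section 5.2 does not say whether an event-specific rule overrides a general one. Section 4.3 lists unacceptable adverse events as a reason to stop treatment but does not settle the order of these rules either.

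**The concern.** The trial is multicentre, and section 10.4 requires every participating institution to work from one version of the protocol. Where that version gives two instructions for one event, two sites can act differently and each can point to the text in support. The decisions concerned are whether a patient stays on drug after a severe toxicity, and at what dose.

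That is first a patient-safety matter. It also touches objective 1.3, which is to characterise toxicity at the recommended phase II dose. Dose received, time on treatment and the number of discontinuations would depend partly on which sentence a site followed.

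**Working it through.** The plan gives no figure on this point, so the check is a comparison of passages, with arithmetic only where it helps.

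**1. Re-escalation.** Take a patient held for hypertension, restarted one level lower, whose blood pressure then settles.
- Table footnote: return to full dose is possible.
- Closing sentence: no re-escalation after a reduction, for any patient.

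Returning to full dose after a reduction is re-escalation. The footnote is permissive, so a site that never re-escalates breaks neither rule. A site that uses the permission breaks the closing sentence, which has no exception. The two cannot both stand as written.

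**2. Length of hold.**
- Table footnote: off protocol therapy once the delay exceeds 2 weeks, 2 × 7 = 14 days.
- General rule: 3 weeks allowed, 3 × 7 = 21 days, with treatment stopped if any grade 3 or 4 toxicity has not resolved by then.

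Grade 3 hypertension is in the held row of the table and is also a grade 3 toxicity, so both rules apply to it. They diverge for holds of 15 to 21 days, a window of 21 − 14 = 7 days. Against the 56 days to the primary response assessment (section 11), the limits are 14/56 = 25% and 21/56 = 37.5% of the period. Grade 4 hypertension raises no such question: the table discontinues therapy at once.

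**3. Grade 4 liver toxicity.** A liver function increase is non-hematologic. If it is grade 4 and drug-related, one bullet takes the patient off study and the other holds treatment and resumes at a lower dose. These actions are incompatible. The overlap does not extend to grade 3 increases or to events not attributed to the drug. Liver enzymes and bilirubin are on the section 5.1 list of possibly related events, so the case is foreseeable, but the protocol gives no rate for grade 4 increases.

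**4. Lead-in dose.**
- Starting dose (section 4.1.2): 400 + 400 = 800 mg/day.
- Lead-in dose: 400 + 200 = 600 mg/day.
- Difference: 800 − 600 = 200 mg/day.

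This equals the first step in the grade 3 non-hematologic bullet and, on the natural reading, in the liver and grade 4 hematologic bullets. The bullet that clearly does not fit the lead-in is the one that takes the patient off study, since no dose follows.

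**5. How often.** The single-agent melanoma trial described in section 2.2 had 2 of 20 patients with hypertension needing intervention. If that rate held:
- both subgroups complete, 37 + 37 = 74 patients: 2/20 × 74 = 7.4;
- both subgroups stop after stage 1, 13 + 13 = 26 patients: 2/20 × 26 = 2.6.

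These are upper illustrations. Under the table, asymptomatic grade 2 hypertension with diastolic pressure below 110 mm Hg is treated while the agent continues, so such cases count as needing intervention but meet neither disputed rule. The cited patients also had refractory disease, whereas this trial excludes prior chemotherapy for metastatic disease.

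**The case against.** The strongest reply is that specific rules normally override general ones. A stricter 2-week limit for hypertension inside a 3-week general ceiling is a common arrangement. The liver bullet names grade 4 expressly, which would have little purpose for drug-related events if the general grade 4 bullet always controlled. This has force for the hold and liver overlaps, and it is why they are the narrower part of the point. It does not remove them, because the section states no precedence and a site could reasonably apply either rule. It does not settle re-escalation, where the general sentence is worded to cover every patient.

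A reader might infer more than the text supports in four ways.
- **That the fixed lead-in dose conflicts with the bullets throughout.** The arithmetic above shows otherwise. The lead-in is also printed at the same list level as the recovery criteria, so some nesting may have been lost in extraction.
- **That skin reactions, which are common with this agent, measure the problem.** The re-escalation and 2-week footnotes belong to hypertension, and the third overlap concerns the liver.
- **That sites will diverge.** The documents show only that they may.
- **That the primary result is compromised.** Section 11.5 keeps eligible patients in the response analysis despite incorrect dosing and makes all treated patients evaluable for toxicity.

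**Conclusion.** The point stands. Section 5.2 is wrong as written on re-escalation: a permission and an unqualified prohibition cover the same act. The hold overlap (grade 3 hypertension held for 15 to 21 days) and the liver overlap (drug-related grade 4 increases) are real but narrow, and a statement of precedence would resolve both. The lead-in is a lesser drafting fault that clearly affects one bullet.

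The consequences fall on patient management, dose received, discontinuations and the toxicity profile. The primary response analysis could be affected only through the dose patients actually receive, not through who is counted. The number of patients affected cannot be estimated from the documents; 2.6 to 7.4 is an upper illustration for hypertension, and it assumes that a rate seen in 20 refractory patients carries over. The conclusion does not depend on that figure, because the contradiction is in the text.

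**What to change.** The sponsor's clinical team should reconcile the bullets, the hypertension table with its footnotes, and the closing sentences of section 5.2, so that each toxicity and grade leads to one action. The section should state whether the event-specific rules for hypertension and liver function override the general rules on re-escalation, length of hold and grade 4 toxicity. Toxicity-specific limits on a hold can remain if that precedence is written down. The lead-in should be reworded so that it does not cover the bullet that takes patients off study. Which rule applies in each case is the sponsor's clinical decision, and this review takes no position on it.

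The cost is an amendment to one section and a memo to sites. Sample size, endpoints and analysis do not change.

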A second phase 1 combination trial administered BAY 43-9006 with carboplatin and paclitaxel (26). BAY 43-9006 was given PO b.i.d. from days 2 to 19 out of a 21 day cycle, and carboplatin (AUC=6) and paclitaxel (225mg/m2) were administered on day 1. Fifteen patients (melanoma (9 pts), lung (1pt), sarcoma (1pt), basal cell (1pt), colon (1pt), esophagus (1pt) and renal cell (1pt)) accrued to 3 dose levels (7 pts at 100 mg, 3 pts at 200 mg, and 1 at 400mg). One grade 3 rash at the 100mg dose level resulted in expanding this cohort. Three patients were treated at the 200mg dose level and one patient at 400mg without DLT. In the first treatment cycle, adverse events (grades 3 and 4) were limited to grade 4 neutropenia (2 pts) and grade 3 events of thrombocytopenia (2), anemia (1), rash (1), hypersensitivity (1), and fatigue (1). All but two patients developed a rash. Among nine patients with melanoma, three partial responses (2 pts at 100 mg and 1 pt at 200 mg) and 5 SDs (2 pts >2 months) were reported. In addition, minor responses were observed in one basal cell carcinoma (at 100 mg after cycle 2 with progression after cycle 4), one SD (at 100 mg for 6+ cycles) in sarcoma, and one SD in renal cell carcinoma (at 200 mg for 3 cycles). Preliminary PK data indicate that there are no significant pharmacokinetic interactions between BAY 43-9006 and paclitaxel/carboplatin.

A single agent trial done at the Royal Mardsen Hospital was presented at the 2004 ASCO meeting. This was a Phase II, single agent trial in patients with Stage IV, refractory melanoma. Patients were treated with BAY 43-9006 400mg po BID for 12 weeks. Responses were assessed at 12 weeks. Twenty patients were enrolled between 10/02 and 4/03. 15 patients had progressive disease before 12 weeks. 4 evaluable patients were reported with 1 PR and 3 SD. 5 patients developed Grade III skin toxicity and 2 patients developed hypertension requiring intervention. No hematolgic toxicity was noted and all toxicities were reversible.

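### Section 5.2 tells a patient whose grade 3 hypertension is controlled on more than one drug both to restart and not to restart, and does not say which rule governs

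*Protocol*

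**What the plan says.** All the provisions are in Protocol section 5.2.

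- **Grade definitions printed under the hypertension table.** Grade 3 is "Grade 3: requiring more than one drug or more intensive therapy than previously". It carries no blood pressure value. Grade 2 is a recurrent, persistent or symptomatic rise for which "monotherapy may be indicated".
- **Hypertension table, asymptomatic grade 2 with diastolic pressure below 110.** "Begin anti-hypertensive therapy and continue agent".
- **Hypertension table, row that includes grade 3.** "Agent should be held* until symptoms resolve". The row also requires a diastolic pressure no higher than 100 mm Hg and calls for antihypertensive treatment. The agent is then restarted one dose level lower. A footnote takes patients off protocol therapy if the delay exceeds 2 weeks.
- **General rule for grade 3 non-hematologic toxicity.** The agent is held, with weekly review, until the toxicity improves to below grade 1 as printed.
- **Conditions for re-treatment, at the head of the section.** After the laboratory limits, other toxicity must be grade 0 or 1.
- **Closing rules, after the hypertension definitions.** A toxicity is given three weeks to clear. The consequence if it does not is stated as follows: "Treatment will be discontinued if any grade 3 or 4 toxicity does not resolve in 3 weeks".

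None of the general rules excepts hypertension, and nothing says whether the table or the general rules take precedence.

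**The concern.** Two scales are used for recovery from the same event. The table uses symptoms and diastolic pressure, measured while the patient takes antihypertensives. The general rules use the toxicity grade, and grade 3 hypertension as printed reflects what treatment the patient needs, not what the pressure is. Treatment can bring the pressure down without lowering the grade for as long as more than one drug is required. A site following the table would then restart the agent, while a site following the general rules would keep it on hold or stop it.

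At stake is consistency of dosing and discontinuation across the participating institutions, and with it the meaning of the toxicity results, which are a secondary endpoint in section 11.1. The event is foreseeable. Hypertension is on the expected adverse event list in section 5.1. In the single-agent melanoma trial at 400 mg BID described in the background, "2 patients developed hypertension requiring intervention" among the 20 enrolled.

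**Working it through.** There is no planned figure to reproduce. The check applies each provision of section 5.2 in turn to defined patients.

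**Patient 1: grade 3, no symptoms, diastolic pressure at or below 100 within the table's 2-week limit, still requiring two drugs.**

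| Provision in section 5.2 | Scale used | Is recovery met? | Instruction |
|---|---|---|---|
| Hypertension table | Symptoms and diastolic pressure | Yes | Restart one dose level lower |
| Grade 3 non-hematologic rule | Grade | No, still grade 3 | Keep holding |
| Re-treatment conditions | Grade 0 or 1 | No, still grade 3 | Do not re-treat |
| 3-week rule, resolve read as a fall in grade | Grade | No | Discontinue at 3 weeks |
| 3-week rule, resolve read as the table's criteria | Symptoms and diastolic pressure | Yes | No action |

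The first three rows already conflict, and they do so without relying on the undefined word in the 3-week rule. The fourth adds a discontinuation, but only on one of two readings. Whether the second row's threshold is below grade 1 or at most grade 1 makes no difference, because this patient is at grade 3.

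**Patient 2: controlled on one drug, none before.** The printed grade 2 covers single-drug treatment. The wording about more than one drug does not make this patient grade 3, and the 3-week rule, which is limited to grades 3 and 4, does not apply.

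**Patient 3: one drug throughout, at higher intensity than before.** Whether grade 3 persists depends on whether the comparison is with baseline or with the last regimen. The protocol does not say, so no firm contradiction can be shown.

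The conflict is therefore firm for Patient 1 only.

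**How often it might arise.** In the background trial 2/20 = 10% had hypertension needing intervention. If that rate applied here (an assumption), 0.10 × 37 = 3.7 patients per subgroup would need some intervention. The source gives neither grade nor number of drugs, so the share resembling Patient 1 cannot be derived. The 3.7 counts any intervention.

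**The case against.** The strongest reply is that a table written for one event governs that event. On that reading its test of symptoms and pressure is what resolution means, and nothing conflicts. In support, the grade 0 or 1 condition stands in a list introduced as recovery of organ function, so applying it to drug-controlled blood pressure is arguable. The grade wording is also the adopted CTCAE scale and not something this trial invented.

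Part of this stands. The reading is reasonable, and it removes the 3-week conflict. But the protocol never states it. The grade 3 non-hematologic rule names a grade threshold and covers hypertension on its face. The closing rule is printed after the table and reaches any grade 3 or 4 toxicity. The sentence that follows forbids re-escalation after a dose reduction, whereas a table footnote allows that full dose may be resumed later. A site cannot safely infer that the closing rules yield to the table. That the scale is adopted explains the wording but does not reconcile the instructions built on it.

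A reader might also think the table circular for patients who enter on an antihypertensive, since adding therapy for a grade 2 rise would make it grade 3. The documents do not require that reading. The grade 2 row speaks of beginning therapy, and a patient who needs a second drug can be graded 3 at presentation and go straight to the hold row.

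**Conclusion.** Section 5.2 contradicts itself for patients with grade 3 hypertension whose pressure is controlled but who still require more than one drug. The table says restart. The grade-based rules say do not restart and, if resolution means a fall in grade, discontinue at 3 weeks. The conclusion rests on the printed definitions and on the absence of any exemption or order of precedence.

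Three stronger readings are tempting and are not supported:

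- **That every patient controlled on treatment stays grade 3.** Control on a single drug is not grade 3 by the more-than-one-drug wording.
- **That patients stopped for hypertension count as treatment failures.** Section 11.5 lists progression, early death and unknown status as failures, not stopping for toxicity. It requires every patient to be assessed for response despite treatment deviations.
- **That the two-stage design loses a calculable amount of power.** This would need both the failure rule above and a known number of affected patients, and the protocol supplies neither.

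The demonstrated effect is that sites may hold or discontinue the agent differently for the same clinical picture. The point is worth correcting because it is foreseeable and cheap to remove.

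**What to change.** Reconcile the provisions in section 5.2 so that each patient with hypertension has one action. State:

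1. whether the hypertension table or the general rules (the grade 3 non-hematologic hold, the grade 0 or 1 condition for re-treatment, and the 3-week discontinuation) govern hypertension;
2. whether resolution of hypertension is judged by CTCAE grade or by the table's symptom and pressure criteria.

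Which rule applies is for the sponsor's clinicians to decide; no view is offered here. The cost is one or two sentences, with no new data or visits. The same amendment can reconcile the 2-week limit in the table with the 3-week limit in the closing rules, and the footnote on resuming full dose with the ban on re-escalation.

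### Section 5.2 leaves two dosing rules unreconciled: a return to full dose after a hypertension reduction, and what follows a drug-related grade 4 liver elevation

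*Protocol*

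**What the plan says.** All the text at issue is in Protocol section 5.2.

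**Re-escalation.** For hypertension that is grade 2 and symptomatic or persistent, or grade 3, or with diastolic pressure of at least 110 mm Hg, the table requires a hold and antihypertensive treatment. When the "agent is restarted, reduce by 1 dose level", and a footnote attached to that instruction adds "May be able to resume full dose later". The section's last sentence, placed after the table and the hypertension grade definitions, reads "No patients should have his / her dose re-escalated following dose reduction".

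**Grade 4 liver events.** One bullet says "Grade 4 non-hematologic toxicity: if study drug related patients should be taken off study". Two bullets further on, another says "Increased liver functions (Grade 3-4): withhold treatment until resolved to < grade 1 toxicity and decrease by 200 mg".

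Neither pair is cross-referenced, and the section states no order of precedence.

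**The concern.** These are dosing and stopping rules that investigators at several institutions must apply to the same kinds of event. Where two rules cover one patient and disagree, sites can treat identical events differently while each points to a written instruction.

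At stake are the exposure of a patient who has already had a hold for raised blood pressure, and the re-exposure of a patient after a drug-related grade 4 liver event. There is also a consistency cost. Section 10.4 provides for one protocol version at all sites and for audit of patient records, and section 11.5 plans descriptive analyses that set aside patients with major protocol deviations. An auditor needs to know which act is the deviation.

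**Working it through.** The protocol states no figure on this point, so the check sets the rules side by side. The only arithmetic is the dose difference.

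**1. Hypertension: patient held, restarted one level lower, pressure now controlled**

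| Site's action | Table footnote | Closing sentence |
|---|---|---|
| Stays at the reduced dose | complies (the footnote only permits) | complies |
| Returns to 400 mg BID | complies | breaches |

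The conflict is therefore one-sided. It arises only when a site uses the permission.

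Dose inputs: the starting dose is 400 mg twice daily (section 4.1.2); the reduced dose named in section 5.2 is 400 mg in the morning and 200 mg in the evening. The hypertension table does not define a dose level. I assume it means this 200 mg/day step.

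- Full dose: 400 + 400 = 800 mg/day
- After one reduction: 400 + 200 = 600 mg/day
- Difference relative to the reduced dose: (800 − 600) / 600 = 0.33

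**2. Grade 4 liver elevation, attributed to study drug, in a patient on full dose**

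Liver tests are non-hematologic: the adverse event list in section 5.1 puts AST, ALT and bilirubin under metabolic/laboratory, not under blood/bone marrow. The event therefore meets the conditions of both bullets.

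| Site's action | Grade 4 non-hematologic bullet | Liver bullet |
|---|---|---|
| Takes patient off study | complies | breaches |
| Holds, then restarts lower after recovery | breaches | complies |

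Here no action satisfies both. Reading the 200 mg decrease as per day, as the neighbouring grade 3 bullet does, the restart dose would be 800 − 200 = 600 mg/day, against no further drug.

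**3. Does specific-over-general settle it?**

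For re-escalation, the table is the more specific text, but the ban is categorical, names no exception and follows directly after the hypertension material. For the liver event, one bullet is more specific by organ and the other by attribution, so the principle does not pick a winner.

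**The case against.** The best case against the liver point is redundancy. The general grade 3 bullet already requires hold and reduction. If the off-study bullet also governed drug-related grade 4 liver events, the liver bullet would add almost nothing for drug-related cases. Its naming of grade 4 therefore looks like a deliberate carve-out. That is a fair reading, but not the only one: the liver bullet would still have work to do for grade 4 elevations not due to the drug, which the off-study bullet does not reach. The carve-out is unlabelled, and the alternative to it is removal from study, so it should be written down.

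The safeguards also count. A hypertension restart requires symptoms resolved and diastolic pressure at or below 100 mm Hg under treatment; uncontrolled pressure leads to a further reduction; more than two reductions, or grade 4, ends therapy. A liver restart requires recovery, and a grade 3 or 4 toxicity unresolved at 3 weeks ends treatment. These limit the harm under either reading but do not say which rule applies.

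Three stronger readings are tempting and not supported:

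- *That section 5.2 gives opposite orders on re-escalation.* The footnote is a permission, and staying at the lower dose breaches nothing.
- *That hold length is a third contradiction*, since the table says "Patients requiring a delay of > 2 weeks should go off protocol therapy" and the closing text says "Patients will be allowed 3 weeks for resolution of toxicity". A tighter limit inside a toxicity-specific table beside a general limit is ordinary drafting, and the specific rule governs.
- *That affected patients can be counted* from the earlier 20-patient single-agent melanoma trial in section 2.2, where "5 patients developed Grade III skin toxicity and 2 patients developed hypertension requiring intervention". That counts hypertension needing intervention. The conflict needs a hold, a reduction, continued treatment and then a decision to re-escalate, and the document gives no rate for that sequence.

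**Conclusion.** Two rules in section 5.2 are unreconciled as written. The footnote permits a return to full dose that the closing sentence forbids, worth 200 mg/day, or one third of the reduced dose, if a dose level is the 200 mg/day step. A drug-related grade 4 liver elevation is both an off-study event and a hold-and-restart event, and no site can obey both bullets.

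The documents give no frequency for either situation, so no number of patients is claimed. The consequence is for patient safety and for uniform dosing across sites, moderated by the existing safeguards.

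A reader might infer damage to the response-rate test or to the toxicity objective (1.3). The document supports neither. Section 11.5 keeps all eligible patients in the main response analysis whatever drug they received and makes all treated patients evaluable for toxicity; section 11.4 summarises all adverse events regardless of cause. The correction should be made because it is safety-relevant and nearly free.

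**What to change.** **Re-escalation.** Delete the footnote that allows full dose to be resumed. This keeps the stricter rule already written for all patients. If the sponsor does want to allow it, add an explicit exception to the closing sentence for reductions made for hypertension, once diastolic pressure is controlled.

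**Grade 4 liver events.** State which bullet governs. The safer option limits the liver bullet to grade 3 and to grade 4 not related to study drug, leaving drug-related grade 4 as off study. The alternative adds to the grade 4 bullet an exception for liver function that points to the liver bullet. This is a clinical choice for the sponsor; the requirement is that the text makes it.

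**Cost.** A wording amendment to one sentence or footnote for each point, issued to all sites. Starting dose, drug supply, visits and sample size do not change.
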